### Population, recruitment, and allocation

The study population will consist of patients diagnosed with seropositive chronic polyarthritis (ICD-10-Code M05) or another chronic polyarthritis (ICD-10-Code M06) with a minimum age of 18, who are being treated by an eligible rheumatologist in Bavaria and are insured with either BKK-LV Bayern or AOK Bayern. Furthermore, participants need to have sufficient German language skills to complete the questionnaires used by the study. Patients with a diagnosis of fibromyalgia (ICD-10-Code M79.7) will be excluded from the study. The probands will primarily be recruited with the assistance of rheumatologists who practice in the study region and will introduce the study to their patients. Furthermore, the study will be promoted in relevant self-help networks, and some patients who gave prior consent to receive such offers will get a postal notification by BKK-LV Bayern or AOK Bayern. The goal is to enrol 440 probands, who will be randomized in equal proportions into the intervention and control groups (each *n* = 220). Based on simulations using the *lme4* package in *R* [24, 25], this sample should allow the identification of even small effects (*f* = 0.1) with adequate statistical power (1 – *β* > 0.8) while considering a possible drop-out rate of 20%.

Prior to patient enrolment, eligible registered rheumatologists in Bavaria will be contacted and asked to participate in the study. After application and confirmation of participation, the rheumatologists will receive comprehensive instructions on their tasks and responsibilities within the study. In addition, psychotherapists can apply to lead an intervention subgroup. Before the study starts, psychotherapists will be selected from the applicants using an assessment process and receive comprehensive training in the content, background, and implementation of the PETRA intervention program (“train the trainer”).

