### Intervention

The intervention is a psychotherapeutically guided, psychoeducational and group-based program designed to strengthen individual health and life skills. It was developed with the help of experienced psychological and medical psychotherapists and aims to improve the emotional, social, and problem-solving skills of each participant by synergistically combining a dynamic-interactional model with disorder-specific coping-oriented perspectives and integrating concepts, ideas, and experiences of existing self-management programs (e.g. the “Gesundheits- und Lebenskompetenz Training [GLK]”, the “HEDE [Health-Ease and Dis-Ease]-Training”, the “Bochumer Gesundheitstraining”, the “Hildesheimer Gesundheitstraining [HGT]”, or the “Zürcher Ressourcen Modell [ZRM]”) [26]. The intervention will be conducted in subgroups of 6–12 participants and led by psychotherapists trained explicitly for this purpose. The main phase consists of 12 2-h sessions over 6 months that address relevant health-associated topics and are conducted at biweekly intervals. Three additional 2-h sessions will take place at monthly intervals, in which the participants can jointly reflect on previous changes and consolidate a viable future perspective for improving their ability to cope with the disease. Each session will begin with an orientation round during which patients check in and prepare for the session. It will end with a closing round where patients can reflect on and share their experiences and insights from the session. This process helps to clarify possible misunderstandings and address any disappointments promptly.

Before the actual start of each 12 session intervention program, there will be a preliminary one-on-one meeting (approximately 45 min) with each participant conducted by the psychotherapist leading the group so they can familiarize with each other, clarify intervention expectations, and discuss possible intervention fears. Then, if necessary, there can be a second meeting.

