The first phase of the intervention program (information phase) comprises six group sessions over 3 months at 2-week intervals, each lasting approximately 2 h. During the first two sessions, the objectives are to get to know each other, build mutual trust, and encourage confidence within the group. Furthermore, the program will be explained, and each patient will voice his or her personal health goals and expectations for the program. The subsequent four sessions (3–6) will address health-associated topics relevant to RA, e.g. nutrition, physical activity, sleep, and stress. Therefore, basic knowledge of each of the topics and its relevance to RA will be shared and subsequently deepened upon using a variety of group exercises, e.g. self-reflective or interactional. In this phase, patients will develop a biopsychosocial understanding of health and disease. This involves recognizing connections between psychological factors (e.g. stress, conflicts, persistent worries) and physical processes, and learning about possible ways to influence and personalize disease management.

The second phase of the intervention (open phase) will also last 3 months with six 2-h group sessions at 2-week intervals. During sessions 7–11, the psychotherapists will refrain from specifying the content of the discussion. Instead, participants will be actively encouraged to express their concerns, such as coping with stress or specific conflicts, and to receive support from the group. The aim of these sessions is to help patients identify personal resources and improve individual disease management, emotion regulation, and conviction of self-efficacy. In addition to the orientation and closing rounds, the structure of each session can vary depending on the topics introduced and discussed by participants and developing group dynamics. Finally, in the last session (12), the group will prepare for the end of the main phase of the program and reflect on progress and improvements.

The third phase of the intervention (sustainability phase) will also last 3 months but contains only three 2-h group sessions at monthly intervals. The psychotherapists will take a more active, leading role again and prepare the patients for detachment from the group and the transition to everyday life without the group. In the last session (15), the group members will reflect and give feedback on the program.

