### Statistical analyses

A central question in the statistical analyses represents the interaction of the intersubject factor group membership (intervention or control group) and the intrasubject factor time of measurement, i.e. the question of the target variables’ different trajectories in the intervention and control group. For longitudinal data analysis, generalized linear mixed models will be estimated, and due to their flexibility, they can model both normally distributed data and count data as dependent variables. In addition, missing values due to drop-outs are less of a problem for mixed longitudinal models compared to analyses of variance, providing a major advantage in analysing clinical programs. For all outcome variables, covariates will be included in the analyses as potential predictors (e.g. age, personality, gender, the severity of illness at baseline).

In the context of these generalized linear mixed models, quasi-Poisson regressions are the preferred method for modelling healthcare-related costs, which are associated with the predictors through log-link functions. Quasi-Poisson regression is preferred over classic Poisson regression for this project because it also allows modelling overdispersion in count data through an additional variance parameter. Immunoendocrine marker levels, questionnaire data and healthcare-related data with an approximated normal distribution, in turn, can be modelled linearly or estimated according to the divergent distribution with a fitted link function. Comparisons between the intervention and control groups will be directly integrated into the mixed regression models with a dichotomous indicator variable, whereby the influence of other covariates in the comparison can be accounted for. Statistical significance is indicated by a *p* value < 0.05. In addition, the Benjamini–Hochberg method will be applied as a correction procedure to avoid the inflation of type I errors in multiple analyses.

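### The described analysis and sample-size statement name no therapy-subgroup term although only the intervention arm is treated in groups; if none is fitted, standard errors are too small whenever subgroup outcomes are correlated

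*Protocol article*

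**What the plan says.** On delivery, the Intervention section states: "The intervention will be conducted in subgroups of 6–12 participants and led by psychotherapists trained explicitly for this purpose". Members of a subgroup share one psychotherapist and 15 two-hour sessions. In the open phase the therapist does not set the topics, and the form of a session may differ "depending on the topics introduced and discussed by participants and developing group dynamics". Under Study design, subgroups start independently once enough patients in a region have enrolled. The Background states that controls do not take part in the program and are only measured on the same schedule.

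On analysis, the Statistical analyses section calls "the interaction of the intersubject factor group membership (intervention or control group) and the intrasubject factor time of measurement" a central question and plans generalized linear mixed models. Arms enter through a two-valued indicator, and the example covariates (age, personality, gender, baseline severity) are all patient characteristics. Study design likewise speaks only of effects within and between individuals. The error rules are "Statistical significance is indicated by a *p* value < 0.05" and "the Benjamini–Hochberg method will be applied as a correction procedure to avoid the inflation of type I errors in multiple analyses".

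On size, Population, recruitment, and allocation says: "The goal is to enrol 440 probands, who will be randomized in equal proportions into the intervention and control groups". It relies on lme4 simulations said to allow "the identification of even small effects (*f* = 0.1") "with adequate statistical power (1 – *β* > 0.8"), with an allowance for 20% drop-out. It names no other allowance. Trial status reports 39 intervention and 34 control patients enrolled when recruitment closed.

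**The concern.** This is a partially nested design: patients are randomised individually, but one arm is then treated in groups. A shared therapist and a shared group process can make members' courses over time resemble each other. The article presents that process as part of how the program works, so zero correlation cannot be taken for granted. If members are analysed as independent, the variance of the intervention-arm estimate is understated. The arm-by-time tests then reject too often under the null hypothesis, and intervals are too narrow. The Benjamini–Hochberg step does not help, because it takes each p value as valid and adjusts only for their number. A power figure computed without the correlation would also be too high for a test that allows for it.

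**Working it through.** **Inputs from the article.** Alpha 0.05 (sidedness not stated; two-sided assumed). 220 per arm planned, or 176 per arm after 20% drop-out. Subgroup size m = 6–12. Realised enrolment 39 versus 34. Number of subgroups: 220/12 to 220/6, about 18–37 as planned; 39/12 to 39/6, about 3–7 as realised.

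**Assumed.** The ICC of a per-patient summary of the trajectory, such as the individual slope. The article gives none, so 0 to 0.10 is shown.

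**Step 1: the stated power.** It cannot be reproduced, because the article gives neither the simulation settings nor the contrast to which f refers.
- Read as a two-group comparison with d = 2f = 0.2, power is 0.47 at 176 per arm.
- Read as a repeated-measures interaction over nine time points with N = 352, it is 0.99 or more.
- Read as a between-group mean over nine time points with N = 352, it is 0.86, 0.71 and 0.59 at within-patient correlations of 0.3, 0.5 and 0.7.

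The claim of more than 0.8 is neither confirmed nor refuted.

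**Step 2: type I error if the subgroup is ignored.** Intervention-arm design effect DE = 1 + (m − 1) × ICC. With equal arms, true SE / naive SE = k = √((1 + DE)/2). Actual alpha = 2 × (1 − Φ(1.96/k)).

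Example, m = 9 and ICC 0.05: DE = 1 + 8 × 0.05 = 1.40; variance ratio (1 + 1.40)/2 = 1.20; k = 1.095; alpha = 7.4%.

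| ICC | m = 6: k, alpha | m = 9: k, alpha | m = 12: k, alpha |
|---|---|---|---|
| 0 | 1.000, 5.0% | 1.000, 5.0% | 1.000, 5.0% |
| 0.01 | 1.012, 5.3% | 1.020, 5.5% | 1.027, 5.6% |
| 0.02 | 1.025, 5.6% | 1.039, 5.9% | 1.054, 6.3% |
| 0.05 | 1.061, 6.5% | 1.095, 7.4% | 1.129, 8.3% |
| 0.10 | 1.118, 8.0% | 1.183, 9.8% | 1.245, 11.5% |

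**Step 3: simulation check.** 10,000 null trials per cell, comparing a t test that ignores subgroups with a test on subgroup means using Satterthwaite degrees of freedom. Values are for m = 6 / 9 / 12.

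| Size | ICC | Subgroup ignored | Subgroup means |
|---|---|---|---|
| 220 v 220 | 0.05 | 6.1 / 7.0 / 8.4% | 4.8 / 4.9 / 5.0% |
| 220 v 220 | 0.10 | 8.1 / 10.1 / 11.8% | 5.2 / 5.1 / 5.0% |
| 39 v 34 | 0.05 | 6.6 / 7.6 / 8.1% | 5.3 / 5.6 / 6.0% |
| 39 v 34 | 0.10 | 8.5 / 9.6 / 11.4% | 5.5 / 5.3 / 5.8% |

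If the reported withdrawals are removed (31 v 32), the subgroup-means test reached up to 6.7%. With so few subgroups the correction is itself approximate.

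**Step 4: power.** Suppose power without clustering were exactly 80%. A test that allows for clustering has power Φ((1.96 + 0.8416)/k − 1.96). At ICC 0.05 this gives 75%, 73% and 70% for m = 6, 9 and 12. Keeping 80% needs 440 × (1 + DE)/2 = 495, 528 and 561 patients. These figures do not describe the test that ignores subgroups: its power is Φ(0.8416/k), about 78% at m = 9 and ICC 0.05, obtained at an alpha of 7.4% instead of 5%.

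**The case against.** The strongest reply is that the article never says patient and time are the only levels. The sentence on arm and time describes the contrast of interest and is not a list of random effects; not even a patient intercept is written out. The models are to be fitted in lme4, which can carry a subgroup effect, and the article says a full protocol is available on request. All of this stands. A reader might infer that the plan excludes subgroup clustering and that type I error therefore exceeds 5%; the text supports neither as fact. What remains is that the article describes the analysis in two places and its size allowance in a third, and each time leaves out the level that its own intervention creates.

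Other limits also stand:
- With no ICC given, the inflation may be negligible: none at 0, and at most 5.6% at 0.01.
- The outcomes run from cytokines to questionnaires to insurance costs, so their ICCs may differ widely. It does not follow that every outcome is affected.
- Stable differences in level between subgroups largely cancel in an arm-by-time contrast. The ICC that matters is that of the trajectory.
- Shared region is not a reason for intervention-only nesting. Patients are randomised individually and both arms come from regional rheumatologists, so region spans the arms. The case rests on therapist and group process.
- A reader might also conclude that the stated power is wrong. With the simulation settings unreported, it can only be called conditional.

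**Conclusion.** The point holds in conditional form. The design groups one arm, and the described analysis and sample-size statement name nothing for it. If no subgroup or therapist term is fitted and the trajectory ICC is positive, standard errors are understated in the direction that makes findings look firmer than they are. The effect on alpha is small at ICC 0.01 and material at 0.05–0.10, where it ranges from 6.5% to 11.5% over subgroup sizes 6–12. Under-recruitment does not remove it: the simulated error at the realised size is similar. These sizes rest on assumed ICCs, two-sided testing, roughly equal subgroups and a single summary per patient.

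**What to change.** In Statistical analyses, state a partially nested model: a random subgroup effect on the treatment trajectory in the intervention arm only, with each control as a singleton. Keep it to one variance component, since about 3–7 subgroups cannot support both a random intercept and a random slope. Use Satterthwaite or Kenward–Roger degrees of freedom for the linear models. These do not carry over directly to the quasi-Poisson cost models, so name a small-sample, cluster-aware alternative there, for example a subgroup-level summary or a cluster permutation or bootstrap method. Report the ICC by outcome. In Population, recruitment, and allocation, state that the power figure is conditional on no subgroup clustering. If a subgroup effect is already in the full protocol or analysis plan, one sentence saying so is enough.

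No new data are needed: under Study procedures and data management, the therapists' attendance lists for their subgroups already reach the evaluating university. The cost is wider intervals and a subgroup variance that will be estimated imprecisely, which the report should acknowledge.

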In contrast, it has been shown that positive emotional experiences, such as mirthful laughter, were followed by changes in cytokine levels connected with a decrease in pro-inflammatory (TNF-α) levels and an increase in anti-inflammatory activity (IL-6, IL-4, IL-1RA) in RA patients [16]. Furthermore, in patients with systemic autoimmune disorders such as RA and systemic lupus erythematosus (SLE), use of the integrative single-case design - specifically developed for the naturalistic investigation of PNI mechanisms in health and disease - revealed a cyclic response pattern in urinary neopterin (an inflammation marker) following emotionally meaningful positive everyday incidents. This pattern ultimately resulted in decreases in neopterin levels after 3–4 days ([17], unpublished data). Based on these findings, it can be suggested that enhancing coping flexibility among RA patients and incorporating stress management programs into RA treatment may have a positive impact on the disease's outcome [18–21].

In a meta-review, Prothero et al. [18] analysed the effect of psychological interventions in patients with RA (8 reviews; 66 studies; 7279 patients) and found immediate postintervention improvements in various categories, namely, pain, fatigue, depression, anxiety, self-efficacy, coping behaviour, physical ability, and functional disability. These beneficial effects remained evident in follow-up assessments for depression (after 8.5 months), coping behaviour (after 8.5 months), self-efficacy (after 15 months), and physical activity (10–14 months). Disease activity and tender or swollen joints showed a delayed improvement after ten weeks and 8.5 months, possibly caused by mediating effects of the postintervention improvements (e.g. depression, coping). Additionally, it has been demonstrated that psychological interventions, including cognitive-behavioural pain management, emotional expression, and stress management, can influence the levels of stress system parameters associated with the immunopathogenesis of RA, such as IL-6, IFN-γ, cortisol, and IL-8 [19–21].

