Furthermore, weekly in-depth psychological interviews (lasting approximately 1 h) using the Incidents and Hassles Inventory (IHI) will be conducted with the patient via online videoconferences. These interviews aim to identify the previous week's negative and positive emotionally meaningful incidents, which will subsequently be rated by a three-person panel following the study period. Additionally, the patients will have weekly appointments with their rheumatologists to determine their DAS 28 (CRP/ESR), SDAI, and CDAI scores.

Using the integrative single-case design, researchers can construct various equidistant time series from biological, psychological, and social datasets. These time series can be statistically analysed to determine their temporal relationships. For instance, one can investigate whether one variable significantly precedes or follows another [36, 37], identify response patterns between variables [17, 38], and determine the duration of temporal delays between variables [39, 40]. For further details on the study design, see [23].

Before the intervention begins, all ten patients participating in the integrative single-case studies will collect data as previously described for the 3-month period leading up to the intervention. In contrast, the follow-up data collection periods are staggered: two patients will be monitored within 1 to 4 months after the intervention ends, four patients within 5 to 8 months after, and four more patients within 9 to 12 months after, each for approximately 1 month. This design allows for the identification of functional changes before and after the intervention, such as alterations in the patients’ psychophysiological response to emotionally meaningful positive and negative incidents.

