In the statistical analyses of the integrative single-case studies, time series variables will be tested on mutual dependency using autoregressive integrated moving average models (ARIMA), cross-correlational analyses and vector autoregressive models (VAR). First, it will be necessary to consider that each time series––psychosocial or biochemical––is governed by two main factors: an internal dynamic structure, giving rise to serial dependency, and serially uncorrelated disturbances. Because of such serial dependencies, an unadjusted cross-correlational analysis may lead to spurious correlations. Therefore, these dependencies will be separated from the disturbances by applying ARIMA filters to the time series. To determine whether one variable significantly precedes and thus predicts another, cross-correlations with the filtered residuals will be computed, both at lag zero (i.e. contemporaneous correlation) and higher lags (up to ± 14) with a significance level of *p* < 0.05.

All planned analyses will be performed with both the newest version of IBM SPSS Forecasting [42] and statistical software *R* [25] using the packages *lme4* (generalized linear mixed-effects models) [24], *tseries* (basic time-series analysis) [43], *forecast* (ARIMA models) [44], *vars* (VAR models) [45], and *ggplot2* (graphical processing) [46].

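### Cross-correlating separately whitened single-case series tests whether two series are related and keeps the onset lag, but can distort the duration and later sign of a response, which the protocol wants to describe

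*Protocol article*

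**What the plan says.** The Statistical analyses section describes each single-case series as "governed by two main factors: an internal dynamic structure, giving rise to serial dependency, and serially uncorrelated disturbances". To avoid spurious correlation, "these dependencies will be separated from the disturbances by applying ARIMA filters to the time series". The use made of the residuals is then stated: "To determine whether one variable significantly precedes and thus predicts another, cross-correlations with the filtered residuals will be computed". This is done "at lag zero (i.e. contemporaneous correlation) and higher lags" up to ±14, "with a significance level of *p* < 0.05". The same section also lists VAR models, without saying what they are to estimate.

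The section Integrative single-case studies says what the time series can be used for. Besides asking whether one variable precedes another, it names the ability to "identify response patterns between variables [17, 38], and determine the duration of temporal delays between variables [39, 40". It also says the design should reveal functional changes from before to after the intervention, such as altered psychophysiological responses to positive and negative incidents. The Background motivates the design with a cyclic neopterin response to positive incidents: "This pattern ultimately resulted in decreases in neopterin levels after 3–4 days".

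**The concern.** The only fully specified procedure (filter, cross-correlate, test each lag) answers whether two series are related. Several of the stated aims concern what the response looks like and how long it lasts. Nothing in the article assigns those aims to another method.

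If the residual cross-correlations are read as a response pattern, two errors are possible. A response lasting several 12-h intervals can shrink towards its first lag. A one-directional response can also be followed by an apparent effect of opposite sign once it has ended. A drop followed by a spurious rise would look like the cyclic pattern that motivates the design. Because the distortion depends on the autocorrelation of the series, a change in autocorrelation from the first to the second monitoring period could pass for a changed response.

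**Working it through.** **Inputs from the protocol article.** Sampling is every 12 h for about one month, so about 30 × 2 = 60 points per period. Lags run to ±14, i.e. ±7 days. A decrease after 3–4 days corresponds to lags 6–8. The per-lag limit at p < 0.05 (taken as two-sided) is ±1.96/√60 = ±0.253.

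**Assumptions, not in the article.** Each series has its own filter; noise is AR(1) with phi 0.4, 0.6 or 0.8; input is white, AR(0.5) or AR(0.7); the true response is −0.4 SD at lags 6, 7 and 8 and zero elsewhere. Filters are AR models of order up to 4 chosen by AIC. The article states no power or error rate for this analysis, so there is no figure to reproduce.

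**Step 1, algebra.** Let y = v(B)x + noise, with x = ψ_x(B)a and y = ψ_y(B)e. With own filters, the residual cross-correlations are proportional to ψ_y⁻¹(B) v(B) ψ_x(B). With the input's filter applied to both series they are proportional to v(B), the response itself.

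**Step 2, hand example.** Take white input (ψ_x = 1) and, for illustration, a response filter of (1 − 0.6B). The pattern becomes:
- lag 6: −0.4
- lag 7: −0.4 + 0.6 × 0.4 = −0.16
- lag 8: −0.16
- lag 9: 0 + 0.6 × 0.4 = +0.24

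The start stays at lag 6, the later lags shrink, and a positive value appears where the true effect is zero. With autocorrelated input, ψ_x partly offsets ψ_y⁻¹. The fitted response filter also depends on the signal, so the net size needs simulation.

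**Step 3, false significant rebound at lag 9 (n = 60).**

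| Input | phi 0.4 | phi 0.6 | phi 0.8 |
|---|---|---|---|
| White | 17% | 31% | 62% |
| AR(0.5) | 3% | 8% | 27% |
| AR(0.7) | 1% | 3% | 9% |

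With the input's filter on both series the rate is at most 2% (nominal upper tail 2.5%). Repeated runs agreed to within a few percentage points; the white-input, phi 0.8 cell ranged from 58% to 65%.

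**Step 4, detection of a true later lag (lag 7).** With white input, own filters find it in 21% / 13% / 7% of series for phi 0.4 / 0.6 / 0.8, against 60–66% with the input's filter. With AR(0.5) input the figures are 44% / 41% / 31%, against 57–80%. With AR(0.7) input and phi 0.6, mean correlations at lags 6–9 are −0.26, −0.23, −0.21 and +0.04, so the shape is largely kept.

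**Step 5, what the method does well.** With no relation between the series, own filters give a per-lag error of 0.039–0.040. Unfiltered correlations give 0.134 (AR 0.5 and 0.7) and 0.198 (both AR 0.7). In further simulations, responses starting at lag 2, 4 or 6 still started there. A smooth response peaking at lag 6 could show its peak at lag 5, so peak and duration can move although the onset does not.

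**Step 6, VAR as a substitute.** At n = 20,000, with a true response of 1 at lags 2–7, a VAR(10) recovered 0.98–1.00 at those lags and −0.02 at lag 8. A VAR(1) missed the response. For two series, a VAR(10) has 2 × 10 + 1 = 21 coefficients per equation and, with 60 points, 60 − 10 = 50 usable rows.

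**The case against.** The residual cross-correlations are given one purpose, deciding whether one variable precedes and predicts another. For that purpose separate whitening is standard, and Step 5 supports it. No sentence says that shape or duration will be read from them. The list of uses in Integrative single-case studies is general, and a cited design paper and the full protocol may say more. VAR is planned, the substudy is explicitly exploratory, and it comprises ten planned patients.

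Much of this stands. A reader might infer that the method removes or reverses the response and its delay, and that false rebounds will therefore be reported. The documents do not support that. The onset lag survives. A separate filter for each series is the natural reading but is not stated literally. The large rebound rates need an input close to white, whereas the article says every series, psychosocial ones included, has serial dependency. With AR(0.7) input the rate is 9% or less.

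What does not fall away is the mismatch. The article fixes a procedure that does not estimate a response, states aims that need one, and links those aims to no other method. VAR is listed for mutual dependency, and an order long enough for lags 6–8 is hard to support with about 60 points. Calling the work exploratory does not reduce a systematic artefact.

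**Conclusion.** The concern holds in a limited form. Cross-correlations of separately filtered residuals are sound for testing dependence and for the onset lag. They are not a sound basis for the duration of a response, the sign of its later lags, or a comparison of these before and after the intervention.

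Under the assumptions above, a false rebound appears in anything from about 1% to 62% of series, against at most 2% with the input's filter. Missed later lags are chiefly a problem where the input is less autocorrelated than the noise. With an unchanged response and white input, moving phi from 0.4 to 0.8 alone raises the rebound rate from 17% to 62%, so a pre/post difference could arise this way. Where a real patient falls in this range cannot be told from the article.

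The result also assumes a relation running from input to response without feedback. It concerns the exploratory single-case studies only and has no bearing on the randomised comparison.

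**What to change.** In Statistical analyses, state that each series is whitened with its own ARIMA filter only to test whether two series are related. State that lag pattern, sign and duration, and their comparison before and after the intervention, come from one of two methods:
- cross-correlations with the input's ARIMA filter applied to both series; or
- a regression of the response on lagged input with ARIMA errors, which the listed *forecast* package or SPSS Forecasting can fit.

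If VAR impulse responses are meant to serve this purpose, say so and give the rule for the lag order.

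The cost is small: a wording change, a little more analysis, no new data and no new software. Some points are lost to lagging, and power at the first response lag is lower in some settings (about 0.68 against 0.83 at phi 0.6 with white input), which is a reason to keep the own-filter test alongside. Trial status reports one single-case study conducted so far, so the change can still be made before most of the data exist.
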